**Natural History of Smoking & Quitting: Longterm Outcomes**

**A. Specific Aims**

At present, some 50 million Americans smoke, these individuals are routinely encouraged to quit, and millions try to quit each year. A great deal is known about how quitting smoking affects a limited set of outcomes. For instance, it is well known that cessation affects the likelihood of lung cancer and heart disease. However, our knowledge of the effects of cessation is narrow. There are major gaps in our understanding of how cessation affects disease processes, mental health, psychosocial adjustment and life satisfaction. Also, little is known about the potential costs or adverse impacts of cessation. Finally, little is known about the precipitants of late relapse. The proposed research is aimed at addressing these gaps in our knowledge. Our cardinal goals are:

*1. To determine the effects of cessation and continued smoking on physiological mechanisms of cardiovascular disease*. We will use state-of-the-art assays such as carotid intima-media thickness, brachial artery endothelial function, and advanced lipoprotein testing to identify the mechanisms via which cessation leads to reduction of cardiovascular disease. We hypothesize that cessation will be followed by an arrest or reversal of atherosclerosis, but that this benefit will also be influenced by other modifiable risk factors (e.g., weight gain, diet, sedentariness, high stress). Our transdisciplinary assessment plan will allow us to produce new knowledge on the impact of cessation on atherosclerosis, and how cessation exerts its effects.1-8

*2. To determine the relation between cessation and mental health outcomes*. While cessation may exacerbate psychiatric symptoms in the short run (e.g., increased depression in the first year post-quit) we hypothesize that, over time, it will lead to decreased symptoms and a reduced likelihood of psychiatric diagnosis. These benefits may occur because smoking per se is a stressor9 because opponent-processes oppose the euphorogenic effects of nicotine10 or for other reasons. In sum we believe that our data will show that quitting smoking is the best thing that people can do to improve their mental health.

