Importantly, we now have highly quantifiable measures (e.g., Carotid IMT) that can, in an accurate and reproducible manner, document atherosclerotic progression or regression. These measures document the anatomical basis for the cardiovascular benefits of smoking cessation reported in epidemiologic studies.40-42 Such measures will also permit insight into the mechanisms of health outcomes, interactions among risk factors, and the subpopulations most affected by particular outcomes. Specifically, we need to know more about how cessation’s relation to atherosclerosis is influenced by individual differences such as gender, level of nicotine dependence and genotype43 and how cessation’s impact is related to changes in other modifiable risk factors such as diet, weight gain, exposure to environmental tobacco smoke, and exercise, which themselves may be affected by cessation.44 For instance, cessation induced weight gain might increase the risk of hypertension, insulin resistance, and hyperlipidemia, all important risk factors for atherosclerosis. Some data do address the impacts of such risk factors,45 but most data in this area are from cross-sectional or short-term cohort studies.1,21,29-32,46,47 Thus, measures such as Carotid IMT and flow-mediated vasodilatation of the brachial artery have rarely been studied prospectively with rich measures of individual differences and other risk factors.

While earlier data on cessation’s impact on carotid IMT showed *arrest* of carotid IMT over three years,1 we believe that more careful assessment of other risk factors may reveal *regression*. Such data have the potential to induce clinicians to change fundamentally their practice patterns. For example, data documenting the arrest of atherosclerotic progression resulting from hyperlipidemia has been associated with an explosive increase in the rate of prescribing statin agents.31 If tobacco cessation produces similar results, clinicians may be motivated to treat tobacco dependence more consistently and intensively. Of course, such data may also motivate more smokers to quit – pictures of atherosclerotic pathology and its arrest due to cessation could powerfully affect smokers’ motivation to quit.48 By integrating prospectively data on changes in smoking habits as well as other key risk factors and objective measures of atherosclerosis, we hope to clarify mechanisms and identify those at greatest risk.

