*Data Acquisition and Preparation.*Data will be inspected on a continuous basis over the course of the study to ensure that data acquisition is satisfactory. Virtually all of the data will be captured via computer entry, scannable forms and palm-top computers. One further data source will be data obtained from medical tests. These typically do not generate computer data files and when they do not, they will be double-entered.

*Data Comparisons.*This study will permit us to address numerous important questions about how quitting smoking and relapse are related to health and psychosocial outcomes, and for whom particular outcomes are especially likely. We cannot outline all of the analyses permitted by this data set. However, we will present analytic plans for several important outcomes. These will reveal the strategies that we will use and the relations to be tested.

We will identify a critical question, use regression methods to identify significant predictors of ultimate endpoints, and then use structural models to explore more complex relations among significant predictors across time. We will assess genetic correlates of critical phenotypes (e.g., nicotine dependence, quitting success, mental health status, and atherosclerosis status and progression) in a parallel research track. We will eventually combine genetic and nongenetic variables in integrated prediction models to determine potential mediators of genetic relations (e.g., via personality) and whether candidate genes predict particular endophenotypes (e.g., smokers reporting escalating or prolonged withdrawal124,125). Construction of genetic models will follow the principles outlined below.

*Predicting Discrete Endpoints.*Many clinicians and others interested in public health will primarily be interested in best-fitting models that predict outcomes (e.g., psychiatric diagnostic outcomes such as depression, or diagnoses such as diabetes, quality of life) at some future point in time. To address the prediction of outcomes at discrete points in time, we will use logistic and multiple regression models (for categorical & continuous dependent variables, respectively) in which ultimate status at Year 2 or 3 is predicted by both prequit and postquit variables.

In testing predictive relations we will follow a general strategy consistent with the model building recommendations made by Hosmer & Lemeshow.277

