All logistic regression models will be developed and tested using procedures and recommendations of Hosmer & Lemeshow.277 For instance, variable selection will start with a careful univariate analysis of each variable, and computation of smoothed scatterplots for continuous variables. After univariate analyses, all independent variables with P-values <0.25 will be candidates for multivariate analyses. Subsequent variable selection will occur in the context of forward selection with a test for backwards elimination. Subsequent to the identification of a multivariate logistic model, the performance of each variable will be evaluated via inspection of the Wald statistic, and the comparison of the multivariate and univariate errors and regression coefficients. If a new model is generated this will be compared with the larger former model via the likelihood ratio test. Eliminated variables will be re-entered to ensure that they have not become valid predictors through the exclusion of other variables. The performance of all continuous variables will be tested for linearity of the logit and any hypothesized (*a priori*) interactions tested. Model fit will be assessed via the Hosmer-Lemeshow test and via area under the ROC curve. Standard model diagnostics will be used (e.g., inspection of leverage values, variance of residuals for covariate patterns). Construction of multiple regression models will be similarly standardized and subjected to appropriate diagnostics.280

Model building will follow strategies frequently used in longitudinal research.1 Thus, *control variables* will be routinely entered (e.g., gender, age, site, ethnicity, Project 1 treatment, SES). Change will be modeled via entry of pretreatment (baseline) measures of the dependent variable and via change scores (which protect against interpretive biases of partialled scores.281,282 Next, relevant *individual differences* will be entered: e.g., nicotine dependence, personality, and genotypes, depending upon the analysis. Then other *modifiable risk factors* will be entered: i.e., measures of diet, alcohol use/abuse, weight/BMI/waist circumference, stressors/distress, exercise, blood pressure, serum lipids, and exposure to second hand smoke. Principal relations will be presented both in univariate and multivariate models. Two-way interactions to be tested will be based upon a priori hypotheses for each tested model.

*Principal Hypotheses*

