Hypothesis 3. Smoking cessation/reduction will lead to improved *quality of life*. We expect continuing smokers to report diminishing QOL levels over the follow-up period (relative to baseline), and we expect exsmokers to report improving QOL. Change will be measured from baseline levels of tested measures (e.g., Quality of Life Questionnaire or other QOL indicator: e.g., 30 day functioning). *Individual differences and control variables*: Improvement in QOL will be inversely related to age.  *Modifiable risk factors:* QOL improvements will be inversely related to postquit heavy drinking days, postquit increase in BMI, post-quit measures of physical health symptoms (CIDI Chronic Conditions & 30 Day Symptoms) and positively related to postquit social support available in the social network. We make a further prediction that much of the improvement in QOL will be mediated by postquit psychiatric symptoms/disorders. We predict that the influence of smoking on QOL will be moderated by postquit weight gain/BMI as those gaining more weight will show a reduced relation between cessation and QOL improvements.11

Hypothesis 4.Smoking relapse late in the follow-up period (>1 yr postquit) will be related to presence of alcohol use in the person’s social network/dyad and to presence of smokers in the social network/dyad and alcohol use. Late relapse will be modeled both as 3-year point-prevalence or latency from 1-year post-quit. *Individual differences and control variables*: Importantly, baseline nicotine dependence will *not* predict late relapse, nor will female gender (although this may be because these factors may have already exerted their influence in the first year of follow-up which we will examine). *Modifiable risk factors:* We expect late relapse likelihood will be positively related to both number of drinking days and heavy drinking days (both postquit), to number of smokers in the social network and contact with such smokers (postquit), and to spousal smoking among partnered participants.

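### No committed model gives the confounder-adjusted overall effect of cessation, because the multivariate models admit post-quit risk factors that cessation may itself change; the gap is sharpest for carotid IMT (Hypothesis 1)

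*Protocol*

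**What the plan says.** Aim 1 (Specific Aims) is "To determine the effects of cessation and continued smoking on physiological mechanisms of cardiovascular disease". Hypothesis 3 is worded causally: cessation or reduction is to lead to better quality of life.

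Under Predicting Discrete Endpoints in the Analytic Plan, "ultimate status at Year 2 or 3 is predicted by both prequit and postquit variables". Models are built in order:
- control variables, entered routinely (the examples are gender, age, site, ethnicity, Project 1 treatment and SES), with the baseline value of the outcome;
- individual differences such as dependence, personality and genotype;
- modifiable risk factors: "measures of diet, alcohol use/abuse, weight/BMI/waist circumference, stressors/distress, exercise, blood pressure, serum lipids, and exposure to second hand smoke".

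Variable selection uses a univariate screen at P<0.25 and then forward selection with backward elimination. This is set out for logistic models, and multiple regression is to be standardised similarly. On reporting, the plan says: "Principal relations will be presented both in univariate and multivariate models".

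The Principal Hypotheses give several risk factors in post-quit form. Hypothesis 1 names weight gain, Hypothesis 2 names post-quit stressors and heavy drinking days, and Hypothesis 3 names "postquit increase in BMI".

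The Background section on physiologic outcomes lists diet, weight gain, environmental smoke exposure and exercise as factors "which themselves may be affected by cessation". Its metabolic part adds that cessation improves glucose tolerance and lipid profile.

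**The concern.** Quitters and continuing smokers are not randomised groups, so an unadjusted comparison is open to confounding. Baseline covariates are the remedy. A factor measured after the quit attempt and changed by it is different: conditioning on it removes the part of the effect that runs through it. What remains is a partial direct effect, which is not the overall consequence of quitting that Aim 1 and Hypothesis 3 ask about.

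The distortion can run either way. Holding weight gain constant could credit cessation with a carotid benefit that quitters who gain weight do not get. Holding improved lipids or lower stress constant could hide a real benefit. For Hypothesis 1, the choice between arrest and regression of atherosclerosis could turn on which model is read.

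**Working it through.** **1. Does any committed model give the overall effect?**

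| Model in the plan | Baseline confounders | Post-quit risk factors | What it estimates |
|---|---|---|---|
| Univariate | none | none | unadjusted contrast |
| Multivariate, final step | yes | yes, if selected | partial direct effect, depending on which factors survive selection |
| Step before the risk-factor block | yes | none | would be close to the overall effect, but the plan does not commit to reporting it or say that smoking status is in it |
| Latent trajectory models | possible | mediation can be modelled | under Structural Models, not used for variables gathered only twice, with carotid IMT as the example |

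**2. The plan's own figure.** Inputs from Power: 300 abstinent, 450 smoking, change of 5.28 in continuing smokers, SD 5.0, a 20% difference, alpha .05 (sidedness not stated).
- Difference = 0.20 × 5.28 = 1.056.
- SE = 5.0 × √(1/300 + 1/450) = 0.3727.
- Two-sided power = Φ(1.056/0.3727 − 1.96) = Φ(0.874) = 0.809.

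This matches the stated .81 (one-sided would give 0.883), so the power figure is not in dispute.

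**3. How far the coefficient could move.** The documents give no mediated share, so the shares below are assumptions. Take 1.056 as the overall effect and hold the SD at 5.0. Adjusted coefficient = 1.056 × (1 − m), where m is positive if the post-quit factors carry the benefit and negative if they oppose it.

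| m | Adjusted coefficient | Power |
|---|---|---|
| +50% | 0.528 | 0.29 |
| +25% | 0.792 | 0.57 |
| +10% | 0.950 | 0.72 |
| 0 | 1.056 | 0.81 |
| −10% | 1.162 | 0.88 |
| −25% | 1.320 | 0.94 |
| −50% | 1.584 | 0.99 |

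**4. Large-sample check with confounding added.** All parameters are assumed: one baseline confounder, about 40% quitting, true overall effect −1.056, one mediator worth 25% of it, 1,000,000 simulated participants.

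| Model | Mediator opposes benefit | Mediator carries benefit |
|---|---|---|
| Cessation only | −1.367 | −1.358 |
| Cessation + confounder | −1.056 | −1.048 |
| Cessation + confounder + mediator | −1.323 | −0.781 |

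Only the middle model recovers the overall effect. The other two are what the plan commits to if the mediator stays in the model.

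**The case against.** **What stands.**
- The overall effect is not the only aim. The Specific Aims also ask how far other modifiable risk factors contribute to outcomes, and a risk-factor-adjusted model answers that.
- Ordered entry would naturally produce a model before the risk-factor block, and nothing says only the last step is shown. A reader might infer that the plan excludes an overall-effect model. It does not; it fails to commit to one.
- Selection may drop some risk factors, and for Hypothesis 1 only weight gain is post-quit by its nature. The timing of the other factors named there is not given.
- The structural models may partly deal with Hypotheses 2 and 3.
- The Limitations section disclaims certainty about causal inference. That does not settle which estimate answers the aim.

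**Stronger readings that the text does not support.**
- A reader might infer that the Background expects adjustment to turn arrest into regression. It says "we believe that more careful assessment of other risk factors may reveal" regression; assessment is not adjustment.
- A reader might infer that the quality-of-life benefit is bound to be adjusted away, since "much of the improvement in QOL will be mediated by postquit psychiatric symptoms/disorders". That is a separately labelled mediation prediction, and those symptoms are not in Hypothesis 3's own list of modifiable risk factors.
- A reader might take the cited cohort's 7.3 micrometre difference (unit prefix lost in the text; read here as micrometres) as an overall effect and inflate it. By the protocol's account under Power, that figure already comes from models controlling for life-style and other risk factors, so it cannot serve that purpose.

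**Conclusion.** The concern holds as a gap in what the plan commits to. The entry rule admits post-quit factors that the protocol itself says may respond to cessation, and the reporting rule secures only an unadjusted and a risk-factor-adjusted estimate. It is firmest for Hypothesis 1, where the trajectory models are expressly unavailable, and weaker for Hypotheses 2 and 3.

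The documents give neither the size nor the direction of the error; the figures in the working show sensitivity only. The conclusion rests on two readings: that the risk-factor block is at least partly post-quit, as the predictor timing and the hypotheses indicate, and that Aim 1 and Hypothesis 3 ask for the overall effect of quitting.

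**What to change.** For Hypothesis 1, and likewise 2 and 3, name as the principal estimate a model with smoking exposure plus pre-quit covariates:
- the baseline outcome;
- the listed control variables;
- baseline nicotine dependence;
- baseline values of the modifiable risk factors.

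Force these in, exempt from the P<0.25 screen and from stepwise deletion. Enter post-quit risk factors only in a second model, labelled as mediation or risk-factor contribution; this still serves the aim on other risk factors. Base any statement about arrest or regression after cessation on the first model.

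The cost is revised wording and one extra model per hypothesis. Table 4 already schedules dependence, diet, activity, weight and blood pressure, waist, blood lipids, alcohol problems and life stress before the quit attempt. It names no separate instrument for second-hand smoke, so the source of that baseline value should be stated.

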*3. To assess the impact of cessation on quality of life (QOL).* We hypothesize that cessation will significantly benefit QOL, but that the extent of benefit will be highly variable across individuals. Most will report enhanced QOL, but a minority will report reductions (e.g., weight gain,11 prolonged depression and/or chronic craving could trump the benefits of quitting).

*4. To identify factors associated with late-occurring relapse.* We hypothesize that late relapse (>1 yr postquit) will be related to presence of tobacco in the person’s social network and to lifestyle factors (e.g., a spouse who smokes, time in smokefree environments, alcohol use). We also hypothesize that late relapse will be unrelated to factors that typically predict short-term relapse (e.g., nicotine dependence, withdrawal symptoms, stressors). While much is known about early relapse, little is known about subsequent relapse. Such late relapse has great public health significance since about 1/3rd 12-14 of those who abstain for one year eventually relapse.

*5. To characterize better the long-term interdependence between smoking and alcohol use and their relations with important health and adjustment domains.* We hypothesize that there will be a relation between smoking and drinking after a quit attempt with heavier drinking predicting a heightened tendency to relapse. We also hypothesize that successful smoking cessation will produce a reduction in drinking frequency. These hypotheses are based on the recognition that tobacco use and alcohol use often co-occur within contexts and within social groups, and the pharmacologic effects of alcohol may foster behavioral dysregulation (e.g., temporal discounting, reduction of executive control, priming of incentive systems).15,16

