**Importance of the Proposed Research to Science and the Public Health**

This research may yield the best long-term information to date on both the physiologic benefits and costs of successful and unsuccessful attempts to quit smoking. It will make important contributions to descriptive psychopathology. It will provide the most fine-grained and accurate information to date on the histories of quitters and relapsers after a quit attempt.

This research will not only characterize the fates of smokers who are successful and unsuccessful in a quit attempt, but will also shed light on mechanisms that mediate observed outcomes. Observed mediational relations may suggest the importance of comprehensive interventions148-150 that can mitigate or prevent negative outcomes of cessation, or enhance positive outcomes. Application of such interventions would be greatly aided by identification of individuals most likely to experience important outcomes of cessation or continued smoking.

This research will also elucidate the precipitants of late relapse - - relapse occurring after the first year of abstinence. Additionally, this research will examine genetic correlates of outcomes such as ability to quit smoking and remain smoke-free, severity of nicotine dependence, severity and patterning of withdrawal symptoms, weight gain, psychiatric diagnoses/symptom profiles, and progression/status of smoking-related disease. Finally, this research may yield information that enhances smokers’ motivation to quit. Smokers may be more likely to make a quit attempt if they believe that smoking cessation will lead to greater life satisfaction, reduced sadness and worry, improved social relations and clinically significant reductions in risk of heart attack and stroke.

It is clear that the information to be gathered is of substantial public health importance. Since 50 million current tobacco users in America are encouraged to quit and approximately 20 million try to quit each year, it is essential to learn how quitting and continued smoking are related to mental health status, disease status and progression, quality of life, and late relapse. It is equally important to be able to identify risk factors for these important outcomes so we can better assist smokers to successfully quit, prevent relapse, and improve mental and physical health.

1. **Preliminary Studies**

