**Expected Abstinence Rates and Attrition**

Based on projections detailed in Project 1, we expect the overall biochemically-confirmed one-week point–prevalence abstinence rates to be 27.6% at six months and 23.6% at 12 months. A survey of some dozen clinical trials (e.g., 151,154,205-207) shows that a typical decline in abstinence rates from 6 to 12 months is about 4%. A similar adjustment was applied to our expected six-month abstinence rates to yield projected 12-month abstinence rates (See Table 2). Comparisons with actual reported 12 month rates 151,153,207-211 shows precedence for these estimates.

*Attrition*. Attrition in Project 2 will be influenced by attrition that occurs during Project 1 (the first year after the quit attempt; see Project 1 for more details). Our attrition expectation for Project 1 suggests one-year attrition rates of 10-20%, based on prior research. For instance, in our most recent clinical trial,13810% of the samplestopped study participation over the 12-month follow-up period. This study is highly relevant to the current attrition estimate since it involved similar assessment and ethnic representation as is proposed for Project 1. That study, however, did not include additional aggressive steps that we will follow to minimize attrition in the current research (see “Steps to reduce attrition” below). In two of our other recent clinical trials having extensive assessment burdens and visit schedules, attrition was about 18% at one year. The attrition projection of 15% over the course of Project 1 therefore, seems reasonable given the retention steps to be employed in the proposed study. Thus, we envision that 15% of 1,520 participants enrolled Project 1 will attrit by month 12, leaving approximately 1,292 available for enrollment in Project 2 (many more than the target enrollment for Project 2 of 900).

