*Smoking outcomes.* Smoking status will be somewhat fluid over the two years of follow-up for subjects in Project 2 as some participants will transition between smoking and abstinence during this time. Research suggests that between 3 – 5% of abstainers at the end of Year one (end of Project 1) will resume smoking each year over the course of follow-up Years 2 & 3 of Project 2.13 Based upon this, we estimate an annual relapse rate of 4% among those confirmed to be successful quitters one year post-quit (See Table 3).

Conversely, data suggest that a significant percentage of those relapsing by Year 1 or later will re-establish abstinence. The large COMMIT longitudinal study suggests a natural quit rate of about 4%/year over several years223. These figures agree with those from the Working Well Trial, the Normative Aging Study, and others showing approximate long term 3% to 5% spontaneous quit rate/year.12,101,224 Some studies such as the Health and Retirement Study113 report higher spontaneous quit rates but the older age range of those participants makes the data less relevant. It is possible that quit rates over Follow-up Years 2 & 3 will be somewhat higher than 4% in this study due to follow-up contacts and the fact that participants entered the study because of an interest in quitting smoking. However, we will use a 4% quit rate as a conservative estimate for both Follow-up Years 2 & 3 (Table 3). We recognize that newly abstinent subjects cannot be treated as continuously abstinent. However, our data will permit continuous measures of smoking over the three-year follow-up period.

Some analyses will use subjects who have been continuously abstinent for the entire 3-year follow-up. Given the abstinence and attrition estimates in Table 3, we expect 300 subjects to fulfill criteria for continuous abstinence at the end of Year 3.

Table 4. Assessment schedules (Orientation visits part of Project 1)

| **Evaluation** | Orientation  (3 Visits) | One Year In-Person Visit | 18-month Phone Follow-Up | Two Year In-Person Visit | 30-month Phone Follow-Up | Three Year In-Person Visit |
| --- | --- | --- | --- | --- | --- | --- |
|
|
| Sign Informed Consent and HIPAA | X |  |  |  |  |  |
| Demographics | X |  |  |  |  |  |
| Smoking History | X |  |  |  |  |  |
| Wisconsin Inventory of Smoking Dependence Motives (WISDM-68) | X | X |  | X |  | X |
| Wisconsin Predicting Relapse in Smoking Measure (WI-PRISM) | X |  |  |  |  |  |

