**E. HUMAN SUBJECTS**

Risks to the Subjects

*Human Subjects Involvement and Characteristics:* While 1520 participants will be enrolled at the baseline of this study (Project 1: Efficacy), only 900 will participate in the proposed follow-up study (Project 2). All individuals who report 7-day point-prevalence abstinence at Week 52 of Project 1 (approximate n = 360) will be invited to participate in the proposed study. The remainder of Project 2 participants (approximate n = 540) will be randomly selected from all relapsed participants from Project 1. All participants will be 18 years of age or older. Inclusion criteria at baseline for Project 1 will be: (1) smoking at least 10 cigarettes/day (on average) for the previous 6 months, (2) a breath sample with a CO level > 9 ppm, (3) being motivated to quit, (4) able to read and write English, (5) agree to respond to EMA prompts throughout the day, (6) plan to remain in the treatment catchment area for at least 12 months after the initiation of treatment, (7) no medical contraindications for use of bupropion (e.g., no uncontrolled hypertension, history of bipolar illness, recent myocardial infarction, recent heavy alcohol use, seizure history, or use of MAO inhibitors or other contraindicated medications), (8) no imminent risk of suicide, (9) no other member of the household is participating, and (10) women are not pregnant and agree to prevent pregnancy during the course of study pharmacotherapy. There will be no restrictions on participation based on sex or race.

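### Hypothesis 4 does not tie late relapse to length of abstinence, and its predictions of no association have neither a margin nor an early-versus-late test

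*Protocol*

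**What the plan says.** Hypothesis 4 (Protocol, Analytic Plan, Principal Hypotheses) gives two outcomes: "Late relapse will be modeled both as 3-year point-prevalence or latency from 1-year post-quit". It does not say which of them governs, and it sets no minimum duration of abstinence at the one-year start of the clock.

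Abstainers enter Project 2 as follows (Protocol, E. Human Subjects): "All individuals who report 7-day point-prevalence abstinence at Week 52 of Project 1 (approximate n = 360) will be invited". The expected number rests on one-week point-prevalence rates of "27.6% at six months and 23.6% at 12 months" (Expected Abstinence Rates and Attrition).

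The section on the importance of the research explains late relapse as "relapse occurring after the first year of abstinence". The background section on delayed relapse likewise speaks of former smokers who have been abstinent for a year.

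On predictors, Hypothesis 4 leads with positive predictions: smokers and alcohol use in the social network, drinking days and spousal smoking. It then expects neither baseline nicotine dependence nor female gender to be a predictor. Goal 4 of the Specific Aims goes further: "We also hypothesize that late relapse will be unrelated to factors that typically predict short-term relapse (e.g., nicotine dependence, withdrawal symptoms, stressors".

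For planning, "we estimate an annual relapse rate of 4% among those confirmed to be successful quitters one year post-quit". This is the middle of a 3-5% range.

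**The concern.** There are two separate problems.

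**Classification.** Post-quit time is counted from the quit attempt, not from the last cigarette. A participant who relapsed early, re-quit a week before the Week 52 contact and smoked again in month 13 would be a late relapse under Hypothesis 4. By the protocol's own description that is an early relapse of a new quit attempt. Such people may carry the usual early-relapse predictors into the late set. The point-prevalence outcome errs in another way: a relapse in month 15 with re-quitting before month 36 counts as success. The protocol expects about 4% of smokers a year to re-establish abstinence, so such cases will occur.

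**Inference.** A prediction of no association cannot be supported by failure to find one when events are few. Nor does a predictor that is significant in year 1 and non-significant afterwards show that its effects differ. At stake is the distinctive part of Aim 4, that late relapse has different causes from early relapse.

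**Working it through.** **1. The protocol's own counts.**
- Abstinent at month 12: 0.236 × 1,520 = 358.7 (stated: about 360).
- Continuously abstinent at Year 3: 360 × 0.91² = 298.1, or 360 × 0.96² × 0.95² = 299.4 (stated: 300).

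The 300 is described as abstinent for the whole three years. It is reached by applying relapse and attrition to all 360 point-prevalence abstainers, so the planning figures treat each of them as abstinent since the quit day.

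**2. Late-relapse events.** Inputs: 360 abstainers; annual relapse r of 3%, 4% or 5%; attrition of 5% a year. With attrition competing, events = 360r + 360(1 − r − 0.05)r.
- r = 3%: 20.7
- r = 4%: 14.4 + 13.1 = 27.5
- r = 5%: 34.2

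Without attrition, 360[1 − (1 − r)²] gives 21.3, 28.2 and 35.1. Among Year 3 completers at 4%, 360 × 0.95² × (1 − 0.96²) = 25.5.

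**3. Precision for a continuous predictor (per SD).** Logistic approximation, two-sided alpha 0.05. The protocol states 0.05 only for its two power analyses; two-sided is assumed here.
- p = 27.5/360 = 0.0764
- SE of log OR = 1/√(360 × 0.0764 × 0.9236) = 0.198
- 95% CI factor = exp(1.96 × 0.198) = 1.48, so an estimate of exactly 1.0 has the interval 0.68 to 1.48
- OR detectable with 80% power = exp(2.8 × 0.198) = 1.74
- Probability of non-significance = Φ(1.96 − ln OR/0.198):

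| Assumed true OR per SD | Non-significant |
|---|---|
| 1.3 | 74% |
| 1.4 | 60% |
| 1.5 | 47% |

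At 21 events the CI factor is 1.55; at 35 events it is 1.42. The odds ratios are assumptions, as the protocol gives none.

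**4. Gender (56% women).** SE = 0.198/√(0.56 × 0.44) = 0.40. The CI factor is about 2.2 and the detectable OR about 3. At 28 events, power is 17% for an OR of 1.5 and 42% for an OR of 2.

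**5. Events needed to show no relation.** With a true OR of 1 per SD, 80% power and a 95% interval inside a symmetric margin m, events ≈ (1.960 + 1.282)²/(ln m)². For 0.80-1.25 this is 10.51/0.0498 ≈ 211. For 0.67-1.5 it is 10.51/0.1644 ≈ 64. Both margins are illustrative.

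**6. If recent quitters are in the risk set.** Suppose a fraction f of the 360 quit recently and a share q of them relapse within two years, with 4% a year in the rest. Events = 360fq + 360(1 − f)(1 − 0.96²). With f from 10% to 30% and q from 30% to 70% (both assumed), the total runs from 36 (10.8 + 25.4) to 95 (75.6 + 19.8). Recent quitters supply 30% to 79% of the events.

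**7. Tools named.** The Analytic Plan screens predictors at P < 0.25, selects forward with a backward check, and uses Wald and likelihood ratio tests. Two-way interactions are limited to a priori ones. Hypotheses 1, 3 and 5 name an interaction or a moderator; Hypothesis 4 names none.

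**The case against.** Several points on the other side have force.

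- **The risk set.** A reader might infer that the protocol fixes the Hypothesis 4 risk set as everyone 7-day abstinent at month 12. It does not. The Week 52 criterion governs enrolment, and Hypothesis 4 names no analysis population. Time-line follow-back will yield continuous abstinence, some analyses are planned on continuously abstinent participants, and the models are to be refined with co-investigators. Both Aim 4 and Hypothesis 4 also gloss late relapse simply as more than a year after quitting. What stands is that the stated outcome carries no abstinence requirement and conflicts with the description given elsewhere.
- **The decision rule.** A reader might infer that non-significance is the declared test of the null. No rule is stated. The protocol promises univariate and multivariate reporting, and Hypothesis 4 notes that dependence and gender may already have acted in year 1, which will be examined. That helps in interpreting a null; it is not a comparison of early and late effects.
- **The place of the null.** It would be wrong to call it the whole of Hypothesis 4. Most of the predictions are positive, and withdrawal and stressors appear only in Aim 4.
- **The event count.** About 28 events assumes the protocol's rate for confirmed quitters. If recent re-quitters are numerous, events exceed 28 and precision improves. The two problems therefore cannot both be pressed at full strength. But the added events would largely be early relapses. Even at 120 events (the protocol's eventual one third of 360), logistic power is 65% for an OR of 1.3 per SD and 44% for a gender OR of 1.5.
- **Point prevalence.** Latency is also planned and captures a relapse followed by re-quitting, so point prevalence need not be dropped.

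**Conclusion.** The concern holds in this limited form. Followed literally, Hypothesis 4 can misclassify early relapses of new quit attempts as late, and its point-prevalence version can miss relapses. How many cannot be computed, because the protocol does not say how many of the 360 are recent quitters. Under its own relapse assumptions, a null result for dependence or gender would not show absence of association, and no early-versus-late test is named. The precision figures assume a two-sided 5% level and a single predictor without covariates.

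The documents do not support the stronger reading that Aim 4 must fail: the positive predictions are unaffected by the missing margin, and the data needed for a sounder analysis will be collected. This is a correction that should be made to one of five hypotheses, one for which the protocol claims no power.

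**What to change.** Revise Hypothesis 4 as follows.

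1. Use time since last cigarette, from the time-line follow-back or abstinence calendar, as the time scale. Alternatively, limit the late risk set to participants with 12 months' continuous abstinence.
2. Make latency the main late-relapse outcome and 3-year point prevalence supplementary.
3. Test the early-versus-late claim directly with a predictor-by-period interaction (first year against later), using the first-year Project 1 data.
4. Report late-period effects with 95% confidence intervals. State that a factor is unrelated only if the interval lies inside a prespecified margin; otherwise report the result as inconclusive.

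The cost is analysis wording only; no new data are needed. Restricting to 12 months' abstinence lowers the number of late events and widens the interval. The time-since-last-cigarette scale avoids discarding participants. The interaction is limited by the same late events, and the claim of no relation will probably have to be reported as inconclusive.
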